#### **6.1.4. Dose Adjustment for Renal Impairment**

Dose adjustment for renal impairment will be made according to  $Cl_{Cr}$  at enrollment and will be adjusted if there are any changes during the study. Additional assessments of serum creatinine or renal function may be performed at the local laboratory at any time during the study, as clinically indicated. NOTE: Although subjects with  $Cl_{Cr}$  of  $\leq 30$  mL/min are initially excluded, if a subject's  $Cl_{Cr}$  decreases to  $\leq 30$  mL/min after enrollment they may remain in the study and the dosage of study drug(s) should be changed accordingly. Placebo infusions should be added as needed to maintain the blind.

- Cefetobiprole: in subjects with moderate renal impairment ( $Cl_{Cr} > 30$  to  $\leq 50$  mL/min) cefetobiprole will be infused at a dose of 500 mg every 12 hours over 120 minutes. In subjects with severe renal impairment ( $Cl_{Cr} > 10$  to  $\leq 30$  mL/min) 250 mg of cefetobiprole will be infused every 12 hours over 120 minutes. Subjects whose  $Cl_{Cr}$  level falls to  $\leq 10$  mL/min are to be discontinued from the study.
- Ceftriaxone: No adjustment of ceftriaxone is recommended in subjects with renal impairment provided the daily dose is 2 g/day or less. To maintain the blind, subjects with  $Cl_{Cr} \leq 50$  mL/min, will receive placebo 2-hour infusions every 12 hours instead of every 8 hours.
- Linezolid: No adjustment is required.
- Cefuroxime axetil: Do not use in subjects with  $Cl_{Cr} < 30$  mL/min.

## **7. COMPLIANCE\***

Qualified staff will administer i.v. study drug and details of each administration will be recorded in the CRF (including date, start time of infusion, dose, and whether the entire dose was administered).

Oral study drug will be dispensed by the pharmacist and the number of doses noted on the CRF. The subject will be instructed to return the study drug container and any remaining study drug at the EOT visit.

---

\* This section of the protocol has been revised. Please refer to the section of this document entitled PROTOCOL AMENDMENTS (Amendment INT-3, 22 December 2006) for a detailed description of the specific changes.

## **8. CONCOMITANT THERAPY**

Concomitant medications are recorded at baseline and throughout the study, in the appropriate section of the CRF. Treatment of pre-existing chronic diseases may be continued during the study.

No other systemic concomitant antibacterial treatment is permitted. The use of antiseptic in a bronchial lavage during the study is not allowed.

Any concurrent treatment that would be contraindicated by the prescribing information for linezolid, ceftriaxone, or cefuroxime axetil is prohibited.

The sponsor must be notified in advance (or as soon as possible thereafter) of any instances in which prohibited therapies are administered.

## **9. STUDY EVALUATIONS**

### **9.1. Study Procedures**

#### **9.1.1. Overview**

The Time and Events Schedule included in the Synopsis summarizes the frequency and timing of efficacy, safety, or other measurements.

The total volume of blood collected for laboratory evaluations throughout this study is approximately 121 mL for each subject (50 mL for safety, 10 mL for mycoplasma and chlamydia titers, 30 mL for blood cultures, 10 mL for repeat blood samples, and up to 21 mL for PK sampling [only 9 mL of blood will be drawn for those subjects participating in the sparse PK sampling, thereby yielding a total blood volume collected of 109 mL]). There will be 3 phases to this study: a prerandomization phase (baseline); a double-blind treatment phase with an EOT visit (within 48 hours after the end of therapy); and a follow-up phase with a TOC/early termination visit 7 to 14 days after the last dose of study drug, and a LFU visit 28 to 35 days after the last dose of study drug.

#### **9.1.2. Prerandomization Phase**

Subjects who have CAP of sufficient severity to necessitate hospitalization and treatment with i.v. antibiotics for at least 3 days (72 hours), will be asked to sign the informed consent form. The investigator will then complete the baseline assessments listed in the Time and Events Schedule and determine if the subject is eligible for enrollment in this study.

#### **9.1.3. Double-Blind Treatment Phase**

The total duration of study drug therapy (i.v. plus oral) for all subjects will be a minimum of 5 days and a target of 7 days. If, in the investigator's opinion, a subject requires additional days of study therapy, the duration of the therapy may be extended (up to a maximum of 10 days) (see Section 6, Dosage and Administration).

If by Day 3, a subject has resolution of signs and symptoms of pneumonia (including fever, WBC, tachypnea, chest X-ray), therapy can be discontinued after all doses on Day 5.

If a subject has a positive blood culture at baseline, they must remain on i.v. study drug for a minimum of 5 days pending results of repeat blood cultures.

Administration of study drug(s) beyond 7 days is recommended only for subjects with persistent signs and symptoms consistent with active infection. These criteria include fever  $\geq 38.3^{\circ}\text{C}$ , circulating WBC count greater than  $10,000 \text{ mm}^3$ , lack of improvement on chest X-ray, continued purulent sputum, or bacteremia at enrollment and at least one positive blood culture on therapy.

If more than 10 days are necessary to complete treatment, therapy may be further extended to a maximum of 14 days for subjects with a history of persistent bacteremia or necrotizing pneumonia.

Dosing will begin on Day 1 after baseline assessments are completed. Subjects will have daily assessments while in the hospital to ensure adequate clinical progress and to ascertain appropriateness for change to oral medication and discharge if desired.

Subjects with serum sodium levels outside of the normal range at baseline or during the study should have their electrolytes measured on a daily basis or more often as clinically indicated until the serum sodium level is within the normal range.

#### **9.1.4. Criteria for Intravenous to Oral Switch\***

Beginning on Day 4 all subjects will be evaluated daily to determine if they meet the criteria for optional switch to oral medication. Once the subject meets the IOS criteria (see below), daily assessments are no longer required. At any time after 3 days (72 hours) of i.v. therapy (between Days 4 and 14), unless the subject was bacteremic upon enrollment, if the subject meets the IOS criteria (see below) for improvement and hospital discharge is desirable, to a location where i.v. therapy is not possible, at the investigator's discretion, the subject may switch from using i.v. to using oral medication. (Change to oral medication is not required.) Assessments will be performed at the time of IOS, before hospital discharge. Subjects with pathogens resistant to cefuroxime axetil will need to complete the full course of i.v. therapy. In order to be eligible for switch to oral medication, a subject must meet ALL of the following criteria:

- Able to swallow and absorb oral medications
- Body temperature improved from baseline (rectal temperature  $\geq 35^{\circ}\text{C}$  and  $\leq 38.8^{\circ}\text{C}$ , axillary temperature  $\geq 35.5^{\circ}\text{C}$  and  $\leq 37.3^{\circ}\text{C}$ , oral temperature  $\geq 36^{\circ}\text{C}$  and  $\leq 37.8^{\circ}\text{C}$ , or tympanic temperature  $\geq 36.5^{\circ}\text{C}$  and  $\leq 38.3^{\circ}\text{C}$ ) for at least 24 consecutive hours in the absence of any antipyretic medications
- White blood cell (WBC) count and bands (%) within the normal range for the laboratory
- Respiratory rate  $\leq 20$  breaths per minute

---

\* This section of the protocol has been revised. Please refer to the section of this document entitled PROTOCOL AMENDMENTS (Amendment INT-3, 22 December 2006) for a detailed description of the specific changes.

JNJ-30982081: Clinical Protocol 30982081-CAP-3001 - Amendment INT-3

- Systolic blood pressure  $\geq 90$  mmHg and pulse  $\leq 100$  beats per minute for at least 24 consecutive hours
- Oxygen saturation of  $\geq 92\%$  by pulse oximeter or  $PO_2 \geq 80$  mmHg on arterial blood gas while subject is breathing room air OR return to documented pre-infection baseline
- Significant improvement in clinical symptoms and signs (cough, sputum production, auscultatory findings, chills, and chest pain) compared with enrollment visit (baseline)
- No clinically significant deterioration observed on the chest X-ray
- Negative blood cultures
  - a. At the enrollment visit (baseline) OR
  - b. If blood cultures obtained at the enrollment visit (baseline) are positive for a pathogen, blood cultures should be repeated and must be negative after a minimum of 3 days (72 hours) incubation.

These criteria for oral switch are consistent with standard medical practice and have been shown to be associated with a positive outcome including in subjects with bacteremic *S. pneumoniae* pneumonia.

At the investigator's discretion, therapy may be stopped anytime after the fifth day of therapy if the infection is considered clinically cured (based on normalization of the clinical signs and symptoms of infection and improvement in the chest X-ray).

If treatment has been extended to 10 days or to 14 days, and it is determined that the subject needs additional antibiotic therapy, the assessments (Visit 5 or 6) will be performed and any significant findings discussed with the Medical Monitor. If the subject does not need additional antibiotic therapy, the EOT assessments should be performed.

### **End-of-Treatment Visit**

End-of-treatment assessments must be performed within 48 hours after the end of therapy. If a subject withdraws prematurely, the TOC/early termination visit assessments must be done at the time of withdrawal.

### **9.1.5. Follow-Up Phase**

#### **Test-of-Cure Visit**

Study assessments will be performed as specified in the Time and Events Schedule at the TOC/early termination visit, which will occur 7 to 14 days after the last dose of study drug. In the event a subject discontinues study drug prematurely, the TOC/early termination visit assessments must be done at the time of study drug discontinuation.

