- g At the investigator’s discretion, therapy may be stopped anytime after the fifth day of therapy when the infection is considered clinically cured (based on normalization of the clinical signs and symptoms of infection and improvement in the chest X-ray and after a minimum of 5 total treatment days).
- h If treatment has been extended to 10 days, and it is determined that the subject needs additional antibiotics, the assessments should be performed and any significant findings discussed with the Medical Monitor. If the subject does not need additional antibiotics, the EOT assessment should be performed.
- i End-of-treatment (EOT) assessments must be performed within 48 hours after the end of therapy.
- j If a subject withdraws prematurely, TOC/early termination visit procedures must be completed at time of withdrawal.
- k Late follow-up by telephone contact unless an examination is needed to evaluate relapse (need for further antibiotic treatment) or abnormalities at TOC assessment.
- l The results of the *legionella* urine antigen test should be available within 24 hours after enrollment. Subjects with proven *legionella* infection should be discontinued from the study and treated appropriately.
- m Women of childbearing potential only. Pregnancy testing will be performed by serum or urine according to local regulations. Additional serum or urine pregnancy tests will be conducted throughout the study in sufficient number, as determined by the investigator or according to local regulations, to establish the absence of pregnancy during the study.
- n The pharmacist will be unblinded to prepare appropriate dosing. An unblinded monitor will perform drug accountability.
- o To include temperature, pulse, respiratory rate, and blood pressure and must be done twice daily at least 8 hours apart, while hospitalized. The vital signs that reflect the highest temperature recorded for the subject on that day should be captured in the case report form (CRF).
- p To be measured at the discretion of the investigator, (e.g., clinically relevant abnormalities, findings, or values or to evaluate relapse).
- q Only clinically significant changes in abnormalities from previous assessment should be recorded.

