### 3.1. Study Design\*

This randomized, double-blind, comparator-controlled, multicenter study is designed to assess the efficacy and safety of ceftobiprole compared with the comparator in subjects 18 years of age or older with CAP of sufficient severity to require hospitalization and treatment with i.v. antibiotics for a minimum of 3 days (72 hours). The study will consist of a prerandomization phase (baseline), a double-blind treatment phase with an end-of-treatment (EOT) visit (within 48 hours after the end of therapy), and a follow-up phase with a TOC/early termination visit 7 to 14 days after the last dose of study drug, and a LFU visit 28 to 35 days after the last dose of study drug. The total duration of the study participation for a subject will be up to 49 days.

---

\* This section of the protocol has been revised. Please refer to the section of this document entitled PROTOCOL AMENDMENTS (Amendment INT-3, 22 December 2006) for a detailed description of the specific changes.

Approximately 670 subjects will be randomized to achieve 266 clinically evaluable subjects receiving ceftobiprole and 266 clinically evaluable subjects receiving the comparator. This trial will be conducted in a manner to ensure that investigators, those administering study drug, and subjects are blinded to treatment regimen. Placebo will be used to maintain the blind for both the cephalosporin (ceftobiprole and ceftriaxone) and linezolid therapies. Central randomization will be used to randomly assign subjects in a 1:1 ratio to receive ceftobiprole or the comparator. Subjects will be stratified by the Pneumonia Outcomes Research Trial (PORT) Severity Index (PSI) score at randomization ( $PSI \leq 90$  versus  $PSI \geq 91$ ; see Attachment 1, PORT Severity Index [PSI]). Subjects will also be stratified by the need for anti-staphylococcal therapy (placebo or linezolid) based on signs, symptoms, and medical history at enrollment.

All subjects should receive a minimum of 3 days (72 hours) of the i.v. study drug(s) and should continue to receive i.v. therapy while hospitalized (see Section 6, Dosage and Administration). At the discretion of the investigator, subjects may receive study drug infusions as outpatients or through a home-care agency, provided they meet all other protocol requirements, but all i.v. study drug infusions must be administered and monitored by a qualified nurse, a qualified member of the study staff, or an infusion specialist.

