## **9.4. Efficacy Criteria**

### **Primary Endpoint**

The clinical cure rate is defined as the ratio of the number of clinically cured subjects to the total number of subjects in the population at the TOC visit.

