### **10.2. Discontinuation of Treatment**

A subject should be discontinued from study treatment if:

- the investigator believes that for safety reasons (e.g., adverse event) it is in the best interest of the subject to stop treatment
- the subject becomes pregnant
- creatinine clearance is <10 mL/min or the subject requires dialysis
- significant myelosuppression occurs during therapy with linezolid/placebo; treatment with linezolid/placebo should be stopped unless it is considered absolutely necessary to continue therapy, in which case, intensive monitoring of blood counts and appropriate management strategies should be implemented
- optic or peripheral neuropathy occurs during therapy with linezolid/placebo; treatment with linezolid/placebo should be stopped

unless it is considered absolutely necessary to continue therapy. Optic and peripheral neuropathy are potential adverse effects of linezolid therapy. Subjects will be educated on symptoms associated with optic neuropathy (e.g., acute blurred vision, vision loss, color loss) and peripheral neuropathy (e.g., paresthesia, sensory loss) and instructed to report them if they occur. If subjects report symptoms of visual impairment, such as changes in visual acuity, changes in color vision, blurred vision, or visual field defect, prompt ophthalmic evaluation is recommended. Visual function should be monitored in all subjects reporting new visual symptoms, regardless of the length of linezolid therapy. Subjects with significant or progressive symptoms will be discontinued from linezolid/placebo therapy and referred for specialty evaluation if symptoms persist.

If a subject discontinues treatment early, TOC assessments should be performed at the time of study drug discontinuation. The subject should be contacted at the LFU visit to obtain MRU information and to follow up on any ongoing adverse events.

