### **11.3.2. Definition of Parameters**

#### **Primary**

- Clinical cure rate, defined as the ratio of the number of clinically cured subjects to the total number of subjects in the population, at TOC visit.

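### Subjects who stop study drug early without withdrawing have their test-of-cure assessment on the day they stop, not 7 to 14 days after the last dose, and a later failure does not revise the primary outcome

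*Protocol*

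**What the plan says.** Protocol Section 3.1 plans "a TOC/early termination visit 7 to 14 days after the last dose of study drug", and Section 9.1.5 (Test-of-Cure Visit) gives the same window. The primary parameter in Section 11.3.2 is tied to that visit: "Clinical cure rate, defined as the ratio of the number of clinically cured subjects to the total number of subjects in the population, at TOC".

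Section 9.1.5 then continues: "In the event a subject discontinues study drug prematurely, the TOC/early termination visit assessments must be done at the time of study drug discontinuation". Section 10.2 says the same: "If a subject discontinues treatment early, TOC assessments should be performed at the time of study drug discontinuation". For later contact with these subjects, Section 10.2 says: "The subject should be contacted at the LFU visit to obtain MRU information and to follow up on any ongoing adverse events".

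Footnote j of the Time and Events Schedule has a similar rule for a different group: "If a subject withdraws prematurely, TOC/early termination visit procedures must be completed at time of withdrawal". The End-of-Treatment Visit text in Section 9.1.4 agrees with footnote j. In the schedule, TOC and early termination are a single visit (Visit 8).

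**The concern.** Same-day assessment makes sense for a subject who is leaving the study. Sections 9.1.5 and 10.2 extend it to subjects who only stop the drug. The protocol separates the two: 10.2 covers stopping treatment, and 10.3 lists loss to follow-up and withdrawn consent as the reasons for withdrawal. A subject under 10.2 is still in follow-up.

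Under Section 9.3.1, Cure can be met by enough improvement that no more antibiotics are needed, with the chest X-ray improved or stable. Seven to 14 days off therapy, that is an observation; on the day dosing ends, it is a forecast. The primary endpoint therefore combines two different measurements, and the proportions depend on who stops early. The TOC cultures have the same timing, so microbiological eradication inherits the problem. An analysis plan cannot repair this, because the visit that would supply the data is never scheduled.

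**Working it through.** **Timing.** The plan states no figure on this point to reproduce, so the check starts from its visit windows.

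- 5-day course (the minimum, Section 6.1.2): TOC at about Day 5 + 7 = 12 to Day 5 + 14 = 19.
- 10-day course: Day 10 + 7 = 17 to Day 10 + 14 = 24.
- Premature stop on Day *d*: TOC on Day *d*, about 0 days after the last dose.

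**Which early stoppers are affected.** Sections 9.3.1 and 11.3.4 sort them as follows.

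- Lack of efficacy and need for other antibiotics after at least 48 hours of therapy: Failure, whenever assessed.
- Stopped for another reason and needs further antibiotics: Unable to evaluate, so a failure in ITT.
- Judged to need no further antibiotics, X-ray improved or stable: Cure. Only this group is affected.

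**Which populations.** ITT includes all of the third group. The CE definition (Section 11.3.1) excludes subjects who are Unable to evaluate *and* have fewer than 5 days of treatment. A premature stop at Day 5 or later that is rated Cure stays in CE on any reading. An earlier one stays only if *and* is read literally, so that both conditions are needed for exclusion.

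**Size per arm.** The protocol gives none of these rates, so all three are assumptions: *e* = share stopping early (5–20%), *c* = share of those rated Cure at the stop (25–50%), *r* = share of those no longer cured 7 to 14 days later (10–30%). Each ITT arm has 670 / 2 = 335 subjects.

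Overstatement of the cure rate = *e* × *c* × *r*:

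- Low: 0.05 × 0.25 × 0.10 = 0.00125, or 0.13 points (335 × 0.00125 = 0.4 subjects).
- Middle: 0.10 × 0.50 × 0.20 = 0.010, or 1.0 point (3.4 subjects).
- High: 0.20 × 0.50 × 0.30 = 0.030, or 3.0 points (10 subjects).

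**Shift in the treatment difference**, with *c* = 0.5 in both arms (ceftobiprole versus comparator):

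- *e* 10% v 10%, *r* 20% v 20%: 0.
- *e* 15% v 10%, *r* 20% v 20%: 0.5 × (0.030 − 0.020) = 0.5 points.
- *e* 20% v 10%, *r* 20% v 20%: 0.5 × (0.040 − 0.020) = 1.0 point.
- *e* 20% v 10%, *r* 30% v 10%: 0.5 × (0.060 − 0.010) = 2.5 points.

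Swapping the arms reverses the sign.

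**Effect on the ITT test if the shift favours ceftobiprole.** Take a comparator ITT cure rate of 0.9 × 0.8 = 72% (planned cure rate times evaluable rate, nonevaluable counted as failures) and a true ceftobiprole rate of 62%, exactly at the 10-point margin. With a shift *b*, the chance of passing is Φ(*b*/SE − 1.96), where SE = √[0.72 × 0.28/335 + (0.62 + *b*)(0.38 − *b*)/335].

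- *b* = 0: 2.5%.
- *b* = 1 point: SE = 0.0360, Φ(0.278 − 1.96) = 4.6%.
- *b* = 2.5 points: SE = 0.0359, Φ(0.697 − 1.96) = 10.3%.

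**The case against.** The best defence is that the protocol's own outcome rules remove most early stoppers from the problem. Anyone who stops early and needs more antibiotics cannot be a false cure. Section 9.1.3 does not foresee a stop on Day 3: even with resolution by then, therapy runs through Day 5. Stopping after 5 or more days because the infection is judged cured is an allowed course and need not count as premature, although the protocol does not define that word. Cure also needs the X-ray condition, and TOC films are read centrally. All of this stands. It limits the point to early stoppers rated Cure.

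A reader might go further in four ways that the documents do not support.

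- *That the bias favours ceftobiprole.* The Phase 2 rates of related vomiting (30%) and nausea (28%) in Section 1.1.1 suggest more tolerability stops, but they come from 750 mg twice daily over 30 minutes, and all 40 subjects completed at least 7 days. Extra stops that need other antibiotics would count as ITT failures, against ceftobiprole.
- *That both coprimary populations are equally exposed.* The CE definition goes on to readmit failures with at least 2 days of treatment, which suggests that other subjects with under 5 days were meant to be excluded. If noninferiority must be shown in both populations, inflation confined to ITT could not by itself produce the claim.
- *That these subjects are never assessed again.* Section 9.3.1 classifies TOC cures at LFU as Cure, Relapse or Unable to evaluate, and 30-day pneumonia mortality is a secondary endpoint. Section 10.2 leaves clinical outcome out of its stated purposes for the LFU contact but does not cancel 9.3.1. What remains true is that neither result revises the TOC outcome.
- *That the shift is the difference in stopping rates times the late non-cure rate.* That treats every early stopper as a Cure. With stops of 15% v 5% and 20% late non-cure it gives 0.10 × 0.20 = 2.0 points; with 25–50% rated Cure it is 0.5 to 1.0 point.

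**Conclusion.** The point holds in limited form and should be fixed. As written, the plan measures the primary endpoint outside its own 7-to-14-day window in subjects who stop drug early but remain in follow-up, and no later TOC is scheduled. The error falls on those rated Cure at the stop. It reaches ITT in every case; its reach into CE depends on the day of stopping and on how the CE definition is read.

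Under the assumed rates, each arm's cure rate is overstated by 0.13 to 3.0 points. The between-arm shift is zero if the arms behave alike and reaches 2.5 points in the most unequal case tried, against a 10-point margin. Its direction is unknown. These sizes are illustrations, because the protocol supplies none of the three rates; the timing conflict itself needs no assumption.

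**What to change.** Reword Sections 9.1.5 and 10.2:

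- A subject who stops study drug early without withdrawing consent has the EOT assessments within 48 hours and the TOC visit (clinical outcome, chest X-ray, cultures) 7 to 14 days after the last dose. A failure for lack of efficacy is carried forward.
- Same-day TOC/early termination procedures apply only to subjects who withdraw from the study, as footnote j and the End-of-Treatment Visit text already say.
- Add clinical outcome to the purposes of the LFU contact in 10.2, in line with 9.3.1.

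The cost is protocol wording and one moved visit for a small group. EOT and TOC already exist, and no treatment rule changes. The drawback is that some early stoppers will not return and will count as ITT failures under Section 11.3.4. That loss is visible and already has a stated rule, whereas an outcome that was never observed at 7 to 14 days cannot be recovered at analysis.
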